## 9. STATISTICAL CONSIDERATIONS

### 9.1 Method of randomisation

Patients will be randomised using a computer-generated algorithm based on random permuted blocks.

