## 9.3 Sample size

As the strategy of PI monotherapy is likely to offer a major advantage in terms of cost (approximately 50% cost reduction from standard-of-care) and possible advantages in terms of long-term tolerability compared to standard-of-care, the trial aims to demonstrate that PI monotherapy is non-inferior to the standard-of-care by a pre-defined amount in terms of the primary endpoint (non-inferiority trial).

The estimation of the sample size is based on the following assumptions using a time-to-event analysis (29):

1. 97% of patients on the standard-of-care arm will maintain all future drug options (i.e. remain free of new resistance mutations) over three years. This figure is based on an approximate 1% annual incidence of the primary study endpoint in three trials of monotherapy – the OK-04 trial (Pulido F et al, AIDS 2008), the MONET trial (Arribas J et al, AIDS 2010) and the MONOI trial (Katlama C et al, 5th IAS Conference 2009).
2. The PI monotherapy arm will be considered “non-inferior” if the upper limit of the 95% confidence interval (2-sided) for the difference in the proportion of patients who maintain all future drug options over three years (standard-of-care – PI monotherapy) is less than 10%. This is consistent with the majority of HIV non-inferiority trials that use a cut-off of 10-15% and with FDA guidelines which recommend a cut-off of 10-12% (28, 31).
3. 85% power to detect non-inferiority according to criterion 2.
4. Recruitment occurs at a uniform rate over 24 months.
5. Total trial duration of 60 months.
6. Cumulative loss to follow-up is approximately 10% by 5 years.

Under these assumptions a total of 554 patients (277 per arm) are required which has been rounded up to 560.

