### 9.5.2 Secondary analyses

The primary analysis will be extended to tabulate individual ART drug options and ART class options which are lost due to the development of resistance. Time-to-event methods will be used to analyse the rate of serious drug- or disease-related complications and for viral load rebound. Also, the frequency of grade III and IV adverse events will be tabulated by body systems and randomised group and the groups will be compared using the  $\chi^2$  test. Repeated measures analysis will be used to compare change in CD4+ cell count from baseline in the allocated strategies.

Patient responses on the MOS-HIV questionnaire will be converted to scores on 11 subscales, ranging from 0 to 100, with higher scores indicating better health (32). The scores are then synthesised into a physical health summary score (PHS) and a mental health summary score (MHS). A general linear mixed model will be used to compare the two groups in terms of changes from baseline in the summary PHS and MHS quality of life indexes over the follow-up period.

The scores on each of the neurocognitive tests will be standardised using demographic-adjusted normative means. This procedure will adjust the data for gender, age, level of education and ethnic background. Briefly, standard scores will be calculated by subtracting the appropriate normative mean from the raw score and then dividing by the appropriate normative standard deviation to give a z score (33). The patient's individual z scores on each test will be averaged to give the patient's neurocognitive function summary score at each

visit. A general linear mixed model will be used to compare the two groups in terms of changes from baseline in the neurocognitive function summary score.

Changes from baseline in the 10-year cardiovascular risk score will also be compared between the two groups using a general linear mixed model.

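### Section 9.5.2 specifies no baseline adjustment for the CD4, quality of life, neurocognitive and cardiovascular change scores; adding it would sharpen these comparisons at almost no cost

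*Combined protocol and SAP*

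**What the plan says.** Section 9.2.2 defines four secondary outcomes as change from baseline: CD4 count, health-related quality of life (PHS and MHS), neurocognitive summary score and cardiovascular risk. Section 9.5.2 then names the analyses.

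- CD4: "Repeated measures analysis will be used to compare change in CD4+ cell count from baseline in the allocated strategies".
- Quality of life: a general linear mixed model "to compare the two groups in terms of changes from baseline in the summary PHS and MHS quality of life indexes".
- Neurocognitive score and 10-year cardiovascular risk: the same type of model, also on changes.

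No model terms are listed for any of them. The only adjustment mentioned is the conversion of neurocognitive test results to z scores using demographic norms. Section 9.5 presents this text as a summary on which a full statistical analysis plan will be based. Section 18 carries the same approach into the extension phase, where CD4 continues to be collected.

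The schedule in section 1.3 shows that the baseline values exist: CD4 at screening and Day 0, MOS-HIV and neurocognitive tests at Day 0, and cardiovascular risk at screening.

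**The concern.** Subtracting baseline fixes the slope of follow-up on baseline at 1. When the true slope is lower, as it is for any measure with error or within-patient fluctuation, subtraction over-corrects and adds noise. A model that includes baseline estimates the slope instead.

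This matters more than usual here because precision for these outcomes was never planned. The only power statement in section 9.3, "85% power to detect non-inferiority according to criterion 2", concerns the resistance endpoint. Yet section 2.5.4 raises neurocognitive decline as a possible risk of monotherapy, section 2.5.1 does the same for cardiovascular risk, and comparing safety is the second objective in section 2.4.1. A needlessly wide interval makes a real difference harder to see and an absence of difference harder to claim.

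Leaving the terms unstated also leaves a choice open in an open-label trial. The adjusted and unadjusted models can give somewhat different answers on the same data, so the choice should be fixed before results by arm are seen.

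**Working it through.** **Inputs.** The plan gives no standard deviation, correlation, power or detectable difference for these outcomes, so there is no figure of its own to reproduce. From section 9.3 I take 560 patients, 280 per arm. The correlation rho between baseline and follow-up is assumed, over 0.3 to 0.9. Baseline and follow-up are given the same SD, set to 1.

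**One follow-up visit.**

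- Change score: variance per patient = 1 + 1 − 2·rho = 2(1 − rho).
- Baseline-adjusted: variance per patient = 1 − rho².
- Ratio: (1 − rho)(1 + rho) / [2(1 − rho)] = (1 + rho)/2.

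The standard error of the difference is √(variance × 2/280). The difference detectable with 80% power at two-sided 5% is (1.960 + 0.842) × SE. For rho = 0.3 the change-score SE is √(1.40 × 2/280) = 0.100, giving 0.280 SD. The adjusted SE is √(0.91 × 2/280) = 0.0806, giving 0.226 SD.

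| Assumed rho | Change variance | Adjusted variance | Ratio | Detectable, change (SD) | Detectable, adjusted (SD) | Power for 0.2 SD: change, adjusted |
|---|---|---|---|---|---|---|
| 0.3 | 1.40 | 0.91 | 0.65 | 0.280 | 0.226 | 52%, 70% |
| 0.6 | 0.80 | 0.64 | 0.80 | 0.212 | 0.189 | 75%, 84% |
| 0.8 | 0.40 | 0.36 | 0.90 | 0.150 | 0.142 | 96%, 98% |
| 0.9 | 0.20 | 0.19 | 0.95 | 0.106 | 0.103 | both above 99% |

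The 0.2 SD difference is illustrative. Dividing 560 by the ratio gives the number of patients the change-score analysis would need for the same precision: 862, 700, 622 and 589.

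**Unequal SDs.** With SDs s₁ at baseline and s₂ at follow-up, the change variance minus the adjusted variance is s₁² + s₂² − 2·rho·s₁s₂ − s₂²(1 − rho²) = (s₁ − rho·s₂)². This is never negative, so the direction does not depend on equal SDs, although the size does.

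**Several visits averaged.** Assume the same correlation between all pairs of visits, and let m = (1 + (k − 1)rho)/k for k follow-up visits. The change variance is m + 1 − 2·rho and the adjusted variance is m − rho². For k = 4:

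- rho 0.3: 0.385/0.875 = 0.44
- rho 0.6: 0.34/0.50 = 0.68
- rho 0.8: 0.21/0.25 = 0.84
- rho 0.9: 0.115/0.125 = 0.92

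**Simulation.** With 280 per arm and 1,500 runs, the variance ratio was 0.75 at rho 0.5 (formula 0.75) and 0.88 at rho 0.8 (formula 0.90). Both estimators were essentially unbiased.

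**Chance imbalance.** The SE of a baseline difference is √(2/280) = 0.085 SD. An imbalance of that size separates the two estimates by (1 − rho) × 0.085, which is about 0.06, 0.03 and 0.02 SD at rho 0.3, 0.6 and 0.8.

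**The case against.** The strongest reply is that silence is not a decision. A reader might infer that the sponsor has chosen an unadjusted analysis. The text does not support that: section 9.5.2 gives an outcome scale and a model family, lists no terms, and belongs to a summary that defers to a full plan. A mixed model on change can include baseline, and it then gives the same treatment effect as modelling the follow-up value. If that is what is intended, nothing is lost. This stands, and it limits the point to an omission in the specification. It does not remove the point, because the summary is the stated basis for the full plan and someone following it literally would fit the weaker model.

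Other stronger readings also fail.

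- **Bias.** A reader might conclude that change scores bias the comparison. Over randomisation they do not. The contrast shifts only conditionally on a realised imbalance, and by the small amounts shown above.
- **All continuous outcomes.** Health care costs are a secondary outcome defined in section 9.2.2 as cost per patient year, not as a change, and fall outside this point.
- **Randomisation.** Section 9.1 says only "Patients will be randomised using a computer-generated algorithm based on random permuted blocks". The lack of a named stratification factor shows little here, since trials would not ordinarily stratify on these scores.
- **Largest gain.** The reduction of 56% (ratio 0.44) needs both a low correlation and a four-visit average. The plan does not say that such an average is the target, so it should not be joined to the one-visit figures as a single range.

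Demographic norming does not answer the point. It places a score relative to people of similar background, but does not account for where that patient started.

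**Conclusion.** The point holds as an inexpensive improvement to the secondary analyses. Sections 9.2.2 and 9.5.2 compare these outcomes as change from baseline and specify no baseline adjustment. Followed literally, that is a valid but less precise analysis.

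At one visit with equal SDs, adjustment removes 35%, 20%, 10% or 5% of the variance for rho of 0.3, 0.6, 0.8 or 0.9, and more if visits are averaged. The formula is firm, but the correlations are assumed and may differ between outcomes. For a measure that tracks as strongly as rho 0.9, the gain is barely noticeable. The conclusion concerns precision and pre-specification only. It does not touch the primary endpoint, the 10% margin or the 560 patients.

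**What to change.** In section 9.5.2 and the full statistical analysis plan, state for each of CD4, PHS, MHS, neurocognitive summary score and cardiovascular risk that the model includes the baseline value of that outcome and its interaction with visit. Equivalently, specify a mixed model with baseline in the response vector and a common baseline mean in both arms. Name the visit that supplies baseline for each outcome; for cardiovascular risk, the schedule in section 1.3 provides only the screening assessment. Results can still be reported as mean change. Settle this before data by arm are examined.

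The cost is one line per model, with no new data and no change to visits or sample size.

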#### **7.2.5 Neurocognitive assessment**

Neurocognitive function will be assessed at Baseline, Week 12, annual visits and the final trial visit using a series of simple neuropsychological tests that can be administered by a clinician or research nurse without specific neuropsychological training, and that will take about 20 minutes to perform. The most common neurocognitive impairments seen in HIV-infected individuals are those that affect frontal sub-cortical functions (23-25). Therefore, the tests have been chosen to detect changes in these functions such as psychomotor speed, memory, executive functions (e.g. processing instructions) and fine motor speed. The following simple, well-established tests will be performed (details provided in Appendix 13):

- Hopkins Verbal Learning Test - Revised. This assesses verbal learning and memory. The examiner reads 12 words and the participant is asked to recall them immediately. The exercise is performed a further two times in exactly the same way. The free recall trials are followed by a recognition test where the examiner reads aloud a list of 24 words and the participant must answer yes or no for each of them depending if the word was or was not included in the original list of 12 words. Finally, after performing the remaining tests listed below and completing the MOS-HIV quality of life questionnaire (i.e. after about 15-20 minutes), the initial free recall test is repeated (without the examiner repeating the list again) to assess delayed memory. A final score based on the number of words recalled or recognised in each part of the test will be calculated (a separate score for immediate and for delayed memory will be produced).
- Colour trails tests (two parts). These assess psychomotor speed and cognitive flexibility within the executive functioning domain (26). In Part 1, participants will be asked to connect a series of encircled numbers in numerical order. In Part 2 they will be also asked to connect 25 encircled numbers alternating between two colours. The score is the time to completion of each of the tasks.

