- Grooved Pegboard test. This assesses psychomotor speed and fine motor function. It is a manipulative dexterity test consisting of 25 holes with randomly positioned slots. Pegs have a key along one side and they must be rotated to match the hole before they can be inserted. Participants are asked to insert the pegs into the slots as rapidly as possible, and the test will be performed with both the dominant and the non-dominant hand. The score is the time to completion of the task (each hand scored separately).

The participant will be given their raw test scores if so desired. The investigator will be provided with a table of normal ranges for each of the tests based on standard population data so that some interpretation of the participant's score can be made, if the participant wishes results to be expressed in that way.

The final evaluation of each participant's neurocognitive function will be done centrally to calculate a neurocognitive function summary score, as described in section 9.5.2.

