## APPENDIX 12: NEUROCOGNITIVE ASSESSMENT TOOLS

### Hopkins Verbal Learning test-revised (HVLt-R)

For this test the examiner will read aloud a list of 12 words and immediately after finishing that, the participant will be asked to freely recall them. The test is performed a further two times asking the participant to recall the words immediately after each reading. After the third exercise of free recall is completed, the examiner will read aloud a list of 24 words which includes the 12 words used for the previous part of the test. The participant will be asked to answer "yes" or "no" as the examiner reads each word if s/he recognises that word as one of the words included in the original 12 word list used for the first part of the test. The list of 24 words to be used in the second part of the test (recognition trial) includes, apart from the 12 "target words", 6 words that are categorically related to the target words. It also includes 6 unrelated words. After completing all the other neuropsychological tests and the MOS-HIV quality of life questionnaire (i.e. after about 15-20 minutes) the examiner will ask the participant to recall the words read at the beginning of the test (without the examiner repeating the list again) in order to assess delayed memory.

Each word recalled is scored during the immediate free recalling section of the test (range 0 – 36) and during the delayed recall test (range 0 – 12). In addition, the total number of correct responses is scored from the recognition section of the test. To control for the effect of practising on repeated administration a different version of the test, with different lists of words, will be used at each visit. A number of different versions of the test are commercially produced (Psychological Assessment Resources Inc).

### Colour Trail Test: Part 1

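### Section 9.5.2 averages word-count and completion-time z scores without reversing the timed tests, so the neurocognitive summary score can hide or mis-sign decline

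*Combined protocol and SAP*

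**What the plan says.** Section 9.5.2 standardises each neurocognitive test against demographic-adjusted norms by "subtracting the appropriate normative mean from the raw score and then dividing by the appropriate normative standard deviation to give a z score". It then combines the results: "The patient's individual z scores on each test will be averaged to give the patient's neurocognitive function summary score". Section 9.2.2 makes change from baseline in this score a secondary outcome, and section 9.5.2 compares the arms on it with a general linear mixed model.

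The raw scores are defined in section 7.2.5:

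- Hopkins Verbal Learning Test: "A final score based on the number of words recalled or recognised in each part of the test will be calculated", and "a separate score for immediate and for delayed memory will be produced".
- Colour Trails, Parts 1 and 2: "The score is the time to completion of each of the tasks".
- Grooved Pegboard, dominant and non-dominant hand: "The score is the time to completion of the task (each hand scored separately".

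Appendix 12 adds a further verbal learning item: "the total number of correct responses is scored from the recognition section of the test". It does not say whether that item enters the average.

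None of these places reverses the sign of the timed tests or says whether a higher summary score is good or bad. The same section does give the direction for the MOS-HIV subscales, where higher is better.

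**The concern.** One formula is applied to scores that run in opposite directions. A patient who gets worse recalls fewer words, so the memory z scores fall, and takes longer, so the timed z scores rise. Averaging the two without aligning them makes the components work against each other, and the result has no consistent meaning.

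This matters because section 2.5.4 raises neurocognitive decline as a theoretical risk specific to PI monotherapy and relies on monitoring function through the trial. Section 7.2.5 makes the centrally calculated summary score the final evaluation of the test battery, and section 9.5.2 gives no other between-arm analysis of it. A score that can shrink or reverse a real difference could give false reassurance on that question.

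**Working it through.** The protocol gives no effect size, SD or power for this outcome, so there is no figure of its own to reproduce. The check applies the stated rule literally.

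**Inputs.** From section 9.5.2: z = (raw - normative mean)/normative SD, with an unweighted average. From section 7.2.5: two memory scores (immediate, delayed) and four timed scores (Colour Trails 1 and 2, Pegboard each hand). The 1 SD decline is an assumption for illustration.

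**Literal score.** With m memory and t timed scores, a memory decline of a SD and a timed decline of b SD, the summary changes by (t·b - m·a)/(m + t). With the timed z scores reversed it would change by -(t·b + m·a)/(m + t).

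| Pattern (m = 2, t = 4) | As written | Timed tests reversed |
|---|---|---|
| Uniform, a = b = 1 | (4 - 2)/6 = +0.33 | -6/6 = -1.00 |
| Memory only, a = 1, b = 0 | -2/6 = -0.33 | -0.33 |
| Timed only, a = 0, b = 1 | +4/6 = +0.67 | -0.67 |

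With six scores the literal score rises when 4b > 2a, that is, when b > a/2.

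**Other countings.** Section 9.5.2 refers only to z scores on each test, so the number of components is open. A uniform 1 SD decline gives (t - m)/(m + t):

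- 3 memory + 4 timed (recognition added): +1/7 = +0.14
- 1 + 2 (one score per test): +1/3 = +0.33
- 1 + 4: +3/5 = +0.60
- 2 + 2: 0.00
- 3 + 2: -1/5 = -0.20

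Reversing the timed scores gives -1.00 in every case.

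**Either direction of reading.** A memory-only decline always moves the literal score down and a timed-only decline always moves it up. If higher means better, the timed-only decline is mis-signed; if higher means worse, the memory-only decline is. With six scores, reading higher as worse gives a uniform decline the right sign but one third of its size.

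**Power illustration, on assumed values.** Take 277 per arm (section 9.3), SD of change 0.8 per test, correlation 0.4 between tests once aligned, a uniform excess decline of 0.15 SD, one change score per patient and no attrition. Only the 277 comes from the protocol.

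- Aligned, six scores: variance 0.64 × (6 + 0.4 × 30)/36 = 0.320; SE = √(0.320 × 2/277) = 0.048; 0.15/0.0481 = 3.12, so power is about 88%.
- As written, six scores: variance 0.64 × (6 - 0.4 × 2)/36 = 0.0924; SE = 0.026; effect +0.05; 0.05/0.0258 = 1.94. A significant difference in the positive direction appears in about 49% of trials.
- As written, other countings on the same assumptions: positive and significant in about 18% (3 + 4), 32% (1 + 2), 73% (1 + 4), 2.5% (2 + 2, which is chance) and under 1% (3 + 2).
- As written, six scores, with SD varied from 0.6 to 1.0 and correlation from 0 to 0.6: about 30% to 77%.

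**The case against.** The strongest reply is that section 9.5 is a summary. Section 9.5 promises a full analysis plan, and the neurocognitive paragraph presents itself as brief and cites an outside reference for the method. Either source may align the signs, and neither is available here. That stands as far as it goes: the documents do not show that the final analysis would be wrong. But section 9.5 also says the full plan will be based on this summary, and the summary gives an explicit formula. A programmer who followed it would produce a misaligned score, and nothing in the protocol would flag it.

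A reader might infer that true decline is always reported as improvement. The documents do not support that. It requires higher to be read as better, which is not stated (although the name of the score suggests it), a particular set of components, and, with six scores, a timed decline greater than half the memory decline.

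A reader might also infer that the score cannot detect harm. That fails too. On the assumptions above, a memory-only excess decline of 0.3 SD changes the six-score average by -0.10 under both methods. The literal score detects it about 97% of the time (0.10/0.0258 = 3.88), against about 55% for the aligned score (0.10/0.0481 = 2.08), because misalignment also cancels shared noise. If the timed tests also decline by 0.1 SD, the literal figure drops to about 25%, against about 93% aligned.

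Nor is this score the only route by which cognitive harm could be seen. HIV encephalopathy is a serious AIDS event (Appendix 7), Grade III and IV events can include cognitive disturbance (Appendix 6), MOS-HIV asks about reasoning, memory and attention (Appendix 5), and investigators receive normal ranges for each test (section 7.2.5). These are coarser, but an error in the composite would not leave all harm unseen.

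**Conclusion.** The concern holds in this form: the rule in 9.5.2, followed as written, averages z scores that run in opposite directions, so memory and speed changes offset and the summary score can hide or mis-sign decline. With the six scores of section 7.2.5, a uniform 1 SD decline comes out at +0.33 instead of -1.00; across plausible countings it is +0.60 to -0.20. These figures follow from the stated formula and need only the assumed size and pattern of decline. Whichever direction is read as better, either a memory-only or a timed-only decline takes the wrong sign.

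The power figures are weaker evidence. They rest on an assumed SD, correlation and effect size and should be read only as a range: from under 1% to about 73% significant in the positive direction, depending on which components enter.

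The outcome is secondary. The primary analysis, the sample size and data collection are unaffected.

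**What to change.** In section 9.5.2, and in the full analysis plan built on it, state three things:

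1. The z scores for Colour Trails 1 and 2 and for both Pegboard hands are multiplied by -1 before averaging.
2. A higher summary score means better function.
3. Exactly which component scores enter the average, including whether verbal learning recognition is one of them.

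Then run the scoring code on a test patient who worsens on every test and confirm that the summary falls. If a power illustration is added, label its SD, correlation and effect size as assumptions and show a range.

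The cost is a few sentences and one code check. The component scores are already collected, so no visit, test or form changes.
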